## Abstract

**Background:**

The prevalence of chronic venous disease is high and occurs more frequently in females. According to the clinical, etiological, anatomical, and pathological classification (CEAP) definition, the reticular veins are included in the C1 class and are mainly associated with aesthetic complaints. Several invasive techniques are used for treatment, including mini phlebectomy, laser ablation, and radiofrequency ablation. However, a wide range of sclerosing agents may serve as minimally invasive alternatives, promoting chemical sclerosis of the vein wall. Although this technique is routinely performed around the world, there is no consensus on the most efficacious and safe chemical agent to be used.

**Methods/design:**

Inclusion criteria are women between 18 and 69 years old with at least 10 cm long reticular veins in the lower limbs, on the outer side of the leg/thigh. Patients with CEAP 2 to 6, or with allergies, pregnancy, performing breastfeeding, or with any dermatologic or clinical problems will be excluded. Patients with venous ultrasound mapping showing involvement of saphenous trunks and/or a deep venous system will also be excluded. Patients will be randomized into two groups, one receiving 75% pure glucose and the other group receiving 0.2% polidocanol diluted in 70% glucose. Just one limb and one session per patient will be performed. The sclerosing agent volume will not exceed 5 mL. Clinical follow-up will include visits on days 7 and 60, always with photographic documentation.

**Discussion:**

This project aims to enroll 96 patients and subject them to a double-blind treatment after the randomization process. The design is intended to evaluate efficacy through a primary end point and safety through a secondary end point. Forty-eight patients have currently been enrolled. Preliminary results for these patients showed that 25 received treatment, 2 were excluded, and 22 returned after 7 days and showed no greater adverse events. To date, establishing efficacy criteria has not been possible, and no patients have reached the 60-day return point. These data may help doctors choose the best chemical agent for the treatment of reticular veins.

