### Patient enrollment and randomization

A convenience sample of patients undergoing treatment for mild varicose veins will be employed. Patient information will be entered into an electronic database, and participants will later be contacted to attend an outpatient evaluation. In the first evaluation, patients who have a reticular vein measuring at least 10 cm long in the outer-side of the leg and/or thigh will be invited to join the study. The sample size was estimated to be 96 treated limbs (see “Statistical analyses”). All subjects will be informed of study risks and will be required to sign an informed consent form approved by the institutional review board. The random allocation schedule will be generated using the computer program Stat Trek (http://stattrek.com/Tables/Random.aspx).

Two groups will be established for the treatment of reticular veins, including either 0.2% polidocanol diluted in 70% glucose or 75% glucose alone. A trained nurse will store all data and remain in charge of arrangements, such as preparing the solutions used in the treatments, throughout the duration of the study. Solutions will be prepared in a specific room (different from the office) using sterile 10 mL syringes. Syringes will be identified according to a random number given to each patient.

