### Statistical analyses

Based on alpha = 0.05, and assuming a standard deviation in the primary endpoint score of 1.5, with 48 participants in each arm, we have >80% power to detect a minimal difference in scores of 0.9. Only one extremity will be included per patient. It is expected that 10% of patients will be lost during follow-up. To promote the most statistically rigorous method, we will use a larger sample size of at least 106 patients. Data will be evaluated either by Student’s *t*-test or non-parametric Mann–Whitney test (if relevant conditions are not met). Categorical variables (e.g., proportions) will be compared between groups using the χ^2^ or Fisher’s exact test when necessary. Scores between the groups will be compared with Mann–Whitney test. All statistical analyses will be performed using STATA® v11 (Stata Corp, College Station, TX, USA). All analyses will be performed on an intent-to-treat basis.

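### The abstract gives an enrolment target of 96, while the statistics section treats 96 as the number before loss to follow-up and commits to at least 106

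*Protocol article*

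**What the plan says.** Three places in the protocol article give a sample size.

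- **Abstract, Discussion:** "This project aims to enroll 96 patients and subject them to a double-blind treatment". This is worded as an enrolment target.
- **Patient enrollment and randomization:** "The sample size was estimated to be 96 treated limbs", followed by a pointer to the statistics section. The allowance for loss is not mentioned here.
- **Statistical analyses:** "with 48 participants in each arm, we have >80% power to detect a minimal difference in scores of 0.9", with the conditions "Based on alpha = 0.05" and "assuming a standard deviation in the primary endpoint score of 1.5". The section goes on: "It is expected that 10% of patients will be lost during follow-up", and for that reason "we will use a larger sample size of at least 106 patients".

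The statistics section also states that "Only one extremity will be included per patient", so 96 limbs and 96 patients are the same count.

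**The concern.** The statistics section separates two numbers: 96 patients who supply the primary score, and at least 106 patients recruited so that about 96 remain after loss. The abstract takes the first number and presents it as the second, which drops the article's own 10% allowance. The enrolment section repeats 96 without saying which of the two it is.

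The stop point for recruitment is at stake. A team or reader working from the abstract would consider the trial complete at 96 enrolled, while one working from the statistics section would continue to at least 106. According to Preliminary results, 48 patients were enrolled, 25 had been treated and none had reached day 60. The target could therefore be settled before any efficacy result was known. Two published targets also make it unclear later whether the trial reached its planned size.

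**Working it through.** **Inputs, all from Statistical analyses unless noted**

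- Difference in score 0.9, SD 1.5, so the standardised difference is 0.9/1.5 = 0.6.
- Alpha 0.05. Sidedness is not stated. Two-sided is assumed, and one-sided is shown as a variant.
- 48 per arm, so 2 × 48 = 96.
- Expected loss 10%.
- Enrolment: at least 106 (Statistical analyses) or 96 (abstract).

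**Step 1. Reproduce the stated power at 48 per arm.**

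Normal approximation: power = Φ(δ / (SD × √(2/n)) − 1.96).

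- SD × √(2/48) = 1.5 × 0.2041 = 0.306
- 0.9/0.306 = 2.94, and 2.94 − 1.96 = 0.98
- Φ(0.98) = 83.6%

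The noncentral t-test gives 82.9%. The stated >80% is confirmed. The smallest n reaching 80% is 44 per arm (normal) or 45 per arm (t-test).

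**Step 2. Reproduce the inflation.**

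- 96 × 1.10 = 105.6, rounded up to 106, which is the article's figure.
- Expected to remain from 106: 106 × 0.90 = 95.4, or 47.7 per arm. T-test power is 82.6%.

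**Step 3. Apply the article's own loss to the abstract's target.**

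- 96 × 0.90 = 86.4 patients, or 43.2 per arm (43 per arm in whole patients, 86 in total).
- Normal approximation at 43 per arm: 1.5 × √(2/43) = 0.3235; 0.9/0.3235 = 2.78; 2.78 − 1.96 = 0.82; Φ(0.82) = 79.4%.

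| Enrolled | Remaining after 10% loss | Power, t-test | Power, normal |
|---|---|---|---|
| 96, no loss (stated basis) | 96 (48 per arm) | 82.9% | 83.6% |
| 106 (Statistical analyses) | 95.4 (47.7 per arm) | 82.6% | – |
| 96 (abstract) | 86.4 (43.2 per arm) | 78.7% | 79.6% |
| 96 (abstract), whole patients | 86 (43 per arm) | 78.5% | 79.4% |

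The shortfall against 80% is therefore between 80 − 79.6 = 0.4 and 80 − 78.5 = 1.5 points. Against the 82.6% expected with 106 enrolled, the t-test loss is 82.6 − 78.5 = 4.1 points. The difference detectable with 80% power by t-test rises from 0.87 at 48 per arm to 0.92 at 43 per arm.

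**Step 4. Variant on sidedness.** With one-sided alpha 0.05, 43 per arm gives 86.8% by t-test, and 43.2 per arm gives 87.4% by the normal approximation. The shortfall then disappears.

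**The case against.** The strongest reply is that the statistics section already settles the matter. It explains how the two numbers relate, and calling the second one larger, and a minimum, shows that 106 replaces 96 for recruitment. On this view the abstract contains one line that was not brought into step, and the design is not in doubt. That is largely right, and it limits the point to reconciling the text. It does not remove the conflict, because the abstract's sentence is worded as an aim to enrol and contradicts the detailed section.

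Several stronger readings are tempting, and the document does not support them.

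- **That 96 is given twice as the recruitment stop.** The enrolment section calls 96 an estimated sample size and points to the statistics section, where 96 is the basis of the power calculation. It lacks a label but does not set a different target.
- **That the power claim is false.** The >80% is claimed for 48 participants per arm, and it reproduces. The article nowhere claims it for 96 enrolled less 10%.
- **That 106 is itself an error.** Dividing instead of multiplying gives 96/0.90 = 106.7, so 107. The article says at least 106, which 107 satisfies, and 106 still leaves about 95 evaluable with 82.6% power. One patient makes no practical difference.
- **That power is lower still because scores are to be compared by the Mann–Whitney test.** Putting a number on this needs a relative efficiency for a 0–5 score with ties, and the article gives none.

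It could also be said that an intention-to-treat analysis keeps all 96. However, the primary score is read from day-60 photographs, and the article itself enlarges the sample for loss, so it counts lost patients as not contributing.

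**Conclusion.** The point holds as an inconsistency in the enrolment target. The abstract's 96 conflicts with the at least 106 in Statistical analyses, and the enrolment section repeats 96 without saying that it is the number before inflation.

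The consequence is modest. Stopping at 96 enrolled would leave about 86 scored patients and power of about 78.5% to 79.6% for a 0.9-point difference, just under the stated >80%. This rests on SD 1.5, equal arms, the article's 10% loss and an assumed two-sided alpha of 0.05; under a one-sided test there is no shortfall. It should be corrected because a recruitment target must be a single number. It does not show that the planned design, with at least 106 enrolled, is underpowered.

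**What to change.** - **Abstract, Discussion:** replace the target of 96 with at least 106 enrolled, to obtain about 96 evaluable.
- **Patient enrollment and randomization:** label the 96 as the evaluable number before the allowance for loss, and give the enrolment figure of at least 106 beside it.
- **If 96 enrolled is the real stop:** change the statistics section instead, and restate power as about 79% for a 0.9-point difference with 86 evaluable.
- **Either way:** state whether alpha 0.05 is one- or two-sided, since the power figure depends on it.

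The first two changes cost only text, because the statistics section already commits to at least 106 and no further recruitment is asked for. The third costs a slightly less favourable power figure.

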**Trial registration:**

ClinicalTrials.gov Identifier: NCT02054325, 3/02/2014.

**Electronic supplementary material:**

The online version of this article (doi:10.1186/1745-6215-15-497) contains supplementary material, which is available to authorized users.

## Background

According to the definition of the clinical, etiological, anatomical, and pathological classification (CEAP), the reticular veins are included in the C1 class and are mainly associated with aesthetic complaints. Several invasive techniques are commonly used for treatment, including mini phlebectomy, laser ablation, and radiofrequency ablation. However, a wide range of sclerosing agents may serve as minimally invasive alternatives, promoting chemical sclerosis of the vein wall. Reticular veins have a diameter no greater than 3 mm and are straight, bluish, and located in the subcutaneous tissue of the lower limbs [1]. They have the same complex etiology of all types of primary venous insufficiency such as hormonal issues, family history, and standing position [2, 3]. However, despite its common occurrence, the condition remains poorly understood [4]. Sclerotherapy is the preferred treatment for some patients because of its simplicity and reproducibility [5, 6], and consists of an intraluminal sclerosing agent application to trigger endothelial injury, with subsequent luminal occlusion of these segments. Many agents, such as hypertonic saline and hypertonic glucose as hyperosmolar sclerosing agents, as well as ethamolin® and polidocanol as detergent agents [5, 7], are known to be effective. Hypertonic osmotic solutions cause dehydration and destruction of endothelial cells. Hypertonic dextrose (or glucose) and sodium tetradecyl sulfate are commonly used due to their low cost and safety [8–10]. Conversely, polidocanol acts as a detergent on vein wall lipids, destroying the cellular cement and causing endothelial maceration; this process effectively occludes the vein [11–14]. Due to its efficacy and manipulability, the use of polidocanol is quite common throughout the world. Usually, it is mixed with a wide variety of diluents, such as distilled water, air, or hypertonic glucose. However, some collateral damage can occur from these mixtures, including necrosis, hyperpigmentation stains, allergic reactions, and systemic disorders. Chest pain, cough, anaphylaxis, scotoma, and gas embolization are unusual, but serious adverse events have already been reported in other studies due to this agent, although these issues are commonly related to miscalculated dosages [15–17].

Chemical sclerotherapy is slightly painful and the discomfort is limited to the puncture site, which warrants a free anesthesia procedure. The procedure is usually well tolerated by patients and has a rapid recovery period. However, the use of sclerotherapy for reticular veins is controversial because of its association with blemishes and other risks. However, evidence of these risks is equivocal [2]. Recent studies have shown that various formations of polidocanol are effective in the performance of sclerotherapy for reticular veins [11]. Results from our study have shown positive effects in the treatment of reticular veins using a 0.2% polidocanol solution and 70% hypertonic glucose. Additionally, there was a low occurrence of stains and no major collateral effects. The Food and Drug Administration approved polidocanol as a medicinal sclerosing agent in the United States in 2010, and was soon followed by several European countries. The formulation of polidocanol described above is available for sclerotherapy in Brazil despite the lack of appropriate scientific literature on this treatment. Therefore, the aim of this study is to assess the benefits and safety of a reticular vein treatment using a formulation of 0.2% polidocanol with 70% hypertonic glucose in Brazilian patients.

### Hypothesis

We hypothesize that 0.2% polidocanol plus 70% hypertonic glucose is superior to 75% hypertonic glucose alone in promoting the disappearance of reticular veins of the lower limbs. Moreover, we hypothesize that 0.2% polidocanol plus 70% hypertonic glucose is not inferior to 75% hypertonic glucose in terms of safety.

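### The safety hypothesis is one of non-inferiority, but the article states no margin or confidence-limit rule and names only tests of difference, which are not designed to establish it

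*Protocol article*

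**What the plan says.** The Hypothesis section of the protocol article sets two hypotheses of different kinds. For efficacy, the mixture of 0.2% polidocanol and 70% glucose "is superior to 75% hypertonic glucose alone in promoting the disappearance of reticular veins of the lower limbs". For safety, the same mixture "is not inferior to 75% hypertonic glucose in terms of safety".

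The Statistical analyses section then fixes the methods:

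- Proportions: "Categorical variables (e.g., proportions) will be compared between groups using the" chi-square test, or Fisher's exact test when needed.
- Scores: "Scores between the groups will be compared with Mann–Whitney test". This covers the 0–5 hyperpigmentation score as well as the efficacy score.
- Sample size: "Based on alpha = 0.05, and assuming a standard deviation in the primary endpoint score of 1.5", and "with 48 participants in each arm", the article states that "we have >80% power to detect a minimal difference in scores of 0.9". This calculation concerns the efficacy score only.

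The section on the secondary (safety) endpoint lists stains, hematomas, edema and phlebitis as the events to be analyzed directly. It adds pain, DVT and the hyperpigmentation score. It does not say which of these carries the non-inferiority conclusion.

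**The concern.** Chi-square, Fisher and Mann–Whitney tests take no difference between the arms as the null hypothesis. Failing to reject that null does not show that the mixture is no worse by more than an acceptable amount. A non-inferiority claim needs such an amount (a margin) and a rule that compares a confidence limit with it. The article states neither, and its sample size was not set with safety in mind.

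This goes beyond detail left to an analysis plan. The article names its tests, and those tests answer a different question from the one its safety hypothesis asks. Because it gives no other rule for judging the hypothesis, a non-significant p-value could be taken as support for it. Safety is half of the stated comparison, and the section on expected adverse effects links reports of gas embolism and DVT to polidocanol. An unsupported claim here would therefore favour the arm about which the article itself raises more concern.

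**Working it through.** **1. The article's own figure.** Inputs from Statistical analyses: n = 48 per arm, difference 0.9, SD 1.5, alpha 0.05 (sidedness not stated; two-sided used here).

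Power ≈ Φ(0.9 / (1.5 × √(2/48)) − 1.960) = Φ(2.939 − 1.960) = Φ(0.979) = 83.6%. The noncentral t gives 82.9%.

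The stated power above 80% reproduces. It concerns efficacy and says nothing about safety.

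**2. How often the named tests miss a true doubling.** The documents give no event rates by arm, so the rates below are assumptions. Let X₁ and X₂ be independent binomial counts with n = 48 and rates p₁ and p₂. The probability of a non-significant result is the sum of P(X₁ = i) × P(X₂ = j) over all pairs (i, j) with p ≥ 0.05. The article does not say when Fisher's test is needed. The last column assumes Fisher if the smallest expected count is below 5, and uncorrected chi-square otherwise.

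| True rates | Fisher only | Chi-square only | Chi-square, Fisher if expected < 5 |
|---|---|---|---|
| 5% vs 10% | 94% | 83% | 92% |
| 10% vs 20% | 82% | 71% | 71% |
| 15% vs 30% | 67% | 57% | 57% |
| 20% vs 40% | 51% | 41% | 41% |
| 30% vs 60% | 20% | 15% | 15% |

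**3. One observed result.** Take 5/48 versus 10/48. The smallest expected count is (5 + 10)/2 = 7.5, so chi-square applies.

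- Risk difference: 10/48 − 5/48 = 10.4 points.
- Chi-square: pooled rate 15/96 = 0.156; z = 0.104 / √(0.156 × 0.844 × 2/48) = 1.405; p = 0.16 (Fisher p = 0.26).
- 95% CI: 10.4 ± 1.96 × 7.33 = −4.0 to +24.8 points.

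The test is non-significant, yet the data are compatible with an excess of nearly 25 points. They would not meet even a 20-point margin.

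**4. What 48 per arm could support.** With equal true rates p, margin m, one-sided alpha 0.025 and 80% power, n per arm = (1.960 + 0.842)² × 2p(1 − p) / m². Both p and m are assumed, to show the range.

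| Control rate | m = 10 points | m = 15 points | m = 20 points |
|---|---|---|---|
| 10% | 142 | 63 | 36 |
| 20% | 252 | 112 | 63 |
| 30% | 330 | 147 | 83 |

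The 95% CI half-width for a risk difference, 1.96 × √(2p(1 − p)/48), is 12 points at 10%, 16 at 20% and 18 at 30%. Of the combinations shown, only a 20-point margin at a 10% control rate fits within 48 per arm.

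**The case against.** **No misreading is announced.** A reader might infer that the plan will declare the mixture not inferior whenever p exceeds 0.05. The article does not say so. It gives no rule for interpreting safety results, and elsewhere it describes the safety aim as comparing, tracking or reporting events. This stands. The supportable statement is that no suitable rule is given, so the misreading is possible.

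**A margin may exist elsewhere.** The full protocol or analysis plan could contain one. This also stands, so the point is limited to what the article states. It does not remove the mismatch, because the named tests would still need a margin rule added or a different analysis put in their place.

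**A doubling is not always missed.** A reader might infer that adverse events could generally double unnoticed. The table does not support that: the miss rate falls from 92% to 15% as the control rate rises from 5% to 30%. The only frequency the article reports is that most patients had a small hematoma by day 7 (Preliminary results, arms not separated). An event already that common cannot double.

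**Fisher-only figures overstate the case.** Fisher's test is planned only when needed, so the last column of the first table is the fairer one.

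**The graded stain measure is not covered.** Hyperpigmentation is also scored 0–5 and compared by Mann–Whitney. If its SD were near 1.5 (an assumption), power for a 0.9-point difference would be roughly 80%. The miss rates above therefore apply to yes/no events only.

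**A significant result in favour of the mixture** would imply that it is not inferior on that variable. That is true, but the hypothesis does not predict it, and it leaves the case of similar arms without a rule.

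**Conclusion.** The mismatch is on the face of the article. The safety hypothesis is non-inferiority, the named tests are tests of difference, no margin or confidence-limit rule is stated, and the sample size rests on efficacy alone. As written, similar or non-significant safety results could not establish the hypothesis.

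The size of the risk depends on event rates that the documents do not give. A missed doubling is likely for control rates up to about 15%, somewhat less than even at 20%, and unlikely at 30%. These figures assume 48 analyzed per arm, a two-sided 0.05 level and Fisher's test only where an expected count is below 5.

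This should be fixed, but it does not threaten the trial. Safety is the secondary endpoint, the efficacy power reproduces, and the primary conclusion is unaffected.

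**What to change.** **Preferred.** Replace the non-inferiority sentence with an estimation objective. Report the risk difference with a 95% CI for each of stains, hematoma, edema and phlebitis, and the between-arm difference with a 95% CI for the hyperpigmentation score. State that a non-significant test will not be interpreted as showing that the mixture is not inferior.

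**Alternative.** Keep the non-inferiority claim for one named safety variable, with a justified margin fixed before unblinding and judged by the confidence limit. The sponsor would have to accept that 48 per arm supports only a wide margin.

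**Cost.** The preferred change needs new wording in the Hypothesis and Statistical analyses sections and a few confidence intervals, with no extra patients or visits. At the time of the article no patient had reached day 60, so on that timing it could be made before final outcomes were known. The downside is a weaker safety claim.
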